### **Adverse Events After the Reporting Period**

After the end of the adverse event reporting period, all deaths, regardless of cause, should be reported through use of the Long-Term Survival Follow-Up eCRF. In addition, if the investigator becomes aware of a serious adverse event that is believed to be related to prior study drug treatment, the event should be reported through use of the Adverse Event eCRF.

---

## **8.3.6 SERIOUS ADVERSE EVENT REPORTING**

Investigators and Institutions will comply with applicable laws, regulations and standards regarding Investigator's and Institution's obligations.

The investigator must record all serious adverse events, complete an SAE Form, and report to DSMC and IRB according to the following timelines:

- All deaths and immediately life-threatening events, whether related or unrelated, will be recorded on the SAE Form and submitted per the instructions below within 24 hours of site awareness.
- Other SAEs, regardless of relationship, will be submitted per the instructions below within 24 hours of site awareness.

SAEs will be submitted to the following email addresses within 24 hours of becoming aware of the event:

To: [[contact]](mailto:[contact])  
[[contact]](mailto:[contact])

Subject: AGICC-ALX148 21CRC01 SAE Report Form

Attach: SAE form completed and signed by the Investigator

After receiving notification of an SAE, AGICC, as the sponsor of the Study, will collect and report SAEs to Investigators, regulatory authorities (with the exception of local IRBs, who local investigators will report to in accordance with applicable requirements), Ethics Committees, or other third parties. AGICC will report to regulatory authorities within 7 calendar days for events that are life-threatening or result in death, and within 15 calendar days for all other events. In addition to the obligations set forth below, AGICC agrees to provide ALX Oncology Ltd, Merck & Co, Inc., & Eli Lilly USA, LLC with a copy of all information AGICC submits to regulators related to any SAEs for the Study Drug(s) that occur during the Study that AGICC has not otherwise provided ALX Oncology Ltd, Merck & Co, Inc., & Eli Lilly USA, LLC.

AGICC will notify Investigators, ALX Oncology Ltd, Merck & Co, Inc., & Eli Lilly USA, LLC of any problems involving risk to Study patients. Investigators will report new safety information to local IRBs in accordance with applicable requirements.

AGICC will notify ALX Oncology Ltd, Merck & Co, Inc., & Eli Lilly USA, LLC within 2 business days but no longer than 3 calendar days of AGICC receiving notification of any SAE experienced by a patient participating in the Study and receiving Study Drug(s) that is possibly related, based on Investigator's assessment, to the Study Drug(s). Serious adverse events should be reported to ALX Oncology Ltd, Merck & Co, Inc., & Eli Lilly USA, LLC using a CIOMS Form or other form acceptable to ALX Oncology Ltd, Merck & Co, Inc., & Eli Lilly USA, LLC. AGICC further agrees to make available promptly to ALX Oncology Ltd, Merck & Co, Inc., & Eli Lilly USA, LLC such records as may be necessary and pertinent for ALX Oncology Ltd,

Merck & Co, Inc., & Eli Lilly USA, LLC to further investigate an adverse event in the Study that is possibly associated with the Study Drug(s).

SAE reports and any other relevant safety information are to be forwarded to the MSD Global Safety [contact]. A copy of all 15 Day Reports and Annual Progress Reports is submitted as required by FDA, European Union (EU), Pharmaceutical and Medical Devices agency (PMDA) or other local regulators. Investigators will cross reference this submission according to local regulations to the MSD Investigational Compound Number (IND, CSA, etc.) at the time of submission. Additionally, investigators will submit a copy of these reports to MSD (Attn: Worldwide Product Safety; [contact]) at the time of submission to FDA.

### **Follow-up of unresolved serious adverse events**

Any SAEs that are unresolved at the time of the initial report submission should be followed up by the investigator for as long as medically indicated, and an updated SAE report submitted at the time new information regarding the event becomes available.

See Section 8.4.2 for Reporting of Unanticipated Problems.

---

## **8.3.7 REPORTING OF PREGNANCY**

### **Pregnancies in Female Patients**

Female patients of childbearing potential will be instructed to immediately inform the investigator if they become pregnant during the study or within 180 days after the last dose of study drug. A pregnancy report should be completed and submitted to AGICC or its designee immediately (i.e., no more than 24 hours after learning of the pregnancy), either by faxing or by scanning and emailing the form using the fax number or email address provided to investigators. Pregnancy should not be recorded on the Adverse Event eCRF. The investigator should discontinue study drug and counsel the patient, discussing the risks of the pregnancy and the possible effects on the fetus. Monitoring of the patient should continue until conclusion of the pregnancy. Any serious adverse events associated with the pregnancy (e.g., an event in the fetus, an event in the mother during or after the pregnancy, or a congenital anomaly/birth defect in the child) should be reported on the Adverse Event eCRF. In addition, the investigator will submit a Clinical Trial Pregnancy Reporting Form when updated information on the course and outcome of the pregnancy becomes available. AGICC will notify ALX Oncology Ltd, Merck & Co, Inc., & Eli Lilly USA, LLC within 2 business days but no longer than 3 calendar days of AGICC receiving notification of pregnancy or lactation exposure.

### **Pregnancies in Female Partners of Male Patients**

Male patients will be instructed through the Informed Consent Form to immediately inform the investigator if their partner becomes pregnant during the study or within 180 days after the last dose of study drug. A Clinical Trial Pregnancy Reporting Form should be completed and submitted to AGICC or its designee immediately (i.e., no more than 24 hours after learning of the pregnancy), either by faxing or by scanning and emailing the form using the fax number or email address provided to investigators. Attempts should be made to collect and report details of the course and outcome of any pregnancy in the partner of a male patient exposed to study drug. An investigator who is contacted by the male patient or his pregnant partner may provide information on the risks of the pregnancy and the possible effects on the fetus, to support an informed decision in cooperation with the treating physician and/or obstetrician. AGICC will notify ALX Oncology Ltd, Merck & Co, Inc., & Eli Lilly USA, LLC LLC within 2 business days but no longer than 3 calendar days of AGICC receiving notification of pregnancy or lactation exposure.

### **Abortions**

Any abortion should be classified as a serious adverse event, recorded on the Adverse Event eCRF, and reported to AGICC immediately (i.e., no more than 24 hours after learning of the event).

### **Congenital Anomalies/Birth Defects**

Any congenital anomaly/birth defect in a child born to a female patient exposed to study drug or the female partner of a male patient exposed to study drug should be classified as a serious adverse event, recorded on the Adverse Event eCRF, and reported to AGICC immediately (i.e., no more than 24 hours after learning of the event).

## **8.4 UNANTICIPATED PROBLEMS**

### **8.4.1 DEFINITION OF UNANTICIPATED PROBLEMS (UAP)**

The Office of Human Research Protection (OHRP) considers unanticipated problems involving risks to participants or others to include, in general, any incident, experience, or outcome that meets **all** of the following criteria:

- Unexpected in terms of nature, severity, or frequency given (a) the research procedures that are described in the protocol-related documents, such as the IRB-approved research protocol and informed consent document; and (b) the characteristics of the participant population being studied;
- Related or possibly related to participation in the research (“possibly related” means there is a reasonable possibility that the incident, experience, or outcome may have been caused by the procedures involved in the research); and

- Suggests that the research places participants or others at a greater risk of harm (including physical, psychological, economic, or social harm) than was previously known or recognized.

This study will use the OHRP definition of UAP.

---

#### 8.4.2 REPORTING OF UNANTICIPATED PROBLEMS

Incidents or events that meet the OHRP criteria for UAPs require the creation and completion of a UAP report. It is the Site PI's responsibility to report UAPs to their IRB per institutional policies. The Lead PI is responsible for reporting the UAP to the IRB and the DSMC. The UAP report will include the following information:

- Protocol-identifying information: protocol title and number, PI's name, and the IRB project number;
- A detailed description of the event, incident, experience, or outcome;
- An explanation of the basis for determining that the event, incident, experience, or outcome represents a UAP;
- A description of any changes to the protocol or other corrective actions that have been taken or are proposed in response to the UAP.

The investigator must record all UAPs, complete a UAP Form, and report to DSMC and IRB within 24 hours of site awareness.

UAPs will be submitted to the following email addresses within 24 hours of becoming aware of the event:

To:            [[contact]](mailto:[contact])  
                     [[contact]](mailto:[contact])

Subject:      AGICC-ALX148 21CRC01 UAP Report Form

Attach:        UAP form completed and signed by the Investigator

After receiving notification of an UAP, AGICC, as the sponsor of the Study, will collect and report UAPs to Investigators, regulatory authorities (with the exception of local IRBs, who local investigators will report to in accordance with applicable requirements), Ethics Committees, or other third parties. AGICC will report to regulatory authorities within 7 calendar days for events that are life-threatening or result in death, and within 15 calendar days for all other events. In addition to the obligations set forth below, AGICC agrees to provide ALX Oncology Ltd, Merck & Co, Inc., & Eli Lilly USA, LLC with a copy of all information AGICC submits to regulators related to any UAPs for the Study Drug(s) that occur during the Study that AGICC has not otherwise provided ALX Oncology Ltd, Merck & Co, Inc., & Eli Lilly USA, LLC.

AGICC will notify Investigators, ALX Oncology Ltd, Merck & Co, Inc., & Eli Lilly USA, LLC of any problems involving risk to Study patients. Investigators will report new safety information to local IRBs in accordance with applicable requirements.

AGICC will notify ALX Oncology Ltd, Merck & Co, Inc., & Eli Lilly USA, LLC within 2 business days but no longer than 3 calendar days of AGICC receiving notification of any UAP experienced by a patient participating in the Study and receiving Study Drug(s) that is possibly related, based on Investigator's assessment, to the Study Drug(s). UAPs should be reported to ALX Oncology Ltd, Merck & Co, Inc., & Eli Lilly USA, LLC using a CIOMS Form or other form acceptable to ALX Oncology Ltd, Merck & Co, Inc., & Eli Lilly USA, LLC. AGICC further agrees to make available promptly to ALX Oncology Ltd, Merck & Co, Inc., & Eli Lilly USA, LLC such records as may be necessary and pertinent for ALX Oncology Ltd, Merck & Co, Inc., & Eli Lilly USA, LLC to further investigate an adverse event in the Study that is possibly associated with the Study Drug(s).

## 8.5 EVENTS OF CLINICAL INTEREST

Selected nonserious and SAEs are also known as events of clinical interest (ECIs) and must be reported to Merck by AGICC.

Events of clinical interest for this study include:

- An overdose of pembrolizumab that is not associated with clinical symptoms or abnormal laboratory results. For purposes of this study, an overdose of pembrolizumab will be defined as any dose of 1,000 mg or greater ( $\geq 5$  times the indicated dose). No specific information is available on the treatment of overdose of pembrolizumab. In the event of overdose, the participant should be observed closely for signs of toxicity. Appropriate supportive treatment should be provided if clinically indicated. If an adverse event(s) is associated with ("results from") the overdose of a Merck product, the adverse event(s) is reported as a serious adverse event, even if no other seriousness criteria are met.
- An elevated AST or ALT lab value that is greater than or equal to 3X the upper limit of normal and an elevated total bilirubin lab value that is greater than or equal to 2X the upper limit of normal and, at the same time, an alkaline phosphatase lab value that is less than 2X the upper limit of normal, as determined by way of protocol-specified laboratory testing or unscheduled laboratory testing.\*

\*Note: These criteria are based upon available regulatory guidance documents. The purpose of the criteria is to specify a threshold of abnormal hepatic tests that may require an additional evaluation for an underlying etiology.

## 9 STATISTICAL CONSIDERATIONS

## 9.1 STATISTICAL HYPOTHESES

### Primary Hypothesis:

1. Evorpaccept (ALX148), cetuximab, and pembrolizumab will demonstrate improved objective response rate (ORR, per RECIST v1.1) compared to historical controls

### Secondary Hypotheses:

1. Evorpaccept (ALX148), cetuximab, and pembrolizumab will demonstrate improved disease control rate (DCR, per RECIST v1.1) compared to historical controls
2. Evorpaccept (ALX148), cetuximab, and pembrolizumab will demonstrate improved duration of response (DOR, per RECIST v1.1) compared to historical controls
3. Evorpaccept (ALX148), cetuximab, and pembrolizumab will demonstrate improved progression-free survival (PFS, per RECIST v1.1) compared to historical controls
4. Evorpaccept (ALX148), cetuximab, and pembrolizumab will demonstrate improved overall survival (OS) compared to historical controls
5. Evorpaccept (ALX148), cetuximab, and pembrolizumab will be safe and tolerable, defined and graded according to the NCI CTCAE v5.0

### Exploratory Hypotheses:

1. Evorpaccept (ALX148), cetuximab, and pembrolizumab will demonstrate improved objective response rate (ORR), disease-control rate (DCR), duration of response (DOR, and progression-free survival (PFS) per iRECIST compared to historical controls
2. After treatment with evorpaccept (ALX148), cetuximab, and pembrolizumab, there will be an enhanced immune response in the peripheral blood and tumor tissue compared to pre-treatment
3. Immune profiles in patients with an objective response to evorpaccept (ALX148), cetuximab, and pembrolizumab will show enhanced immune response in the tumor and peripheral blood compared to non-responders (by RECIST v1.1 and iRECIST)
4. Objective response rate will not correlate with pre-treatment PD-L1 tumor expression by immunohistochemistry (by RECIST v1.1 and iRECIST)
5. Objective response rate will not correlate with pre-treatment EGFR tumor expression by immunohistochemistry (by RECIST v1.1 and iRECIST)
6. Objective response rate will not correlate with pre-treatment CD47 tumor expression by immunohistochemistry (by RECIST v1.1 and iRECIST)
7. Objective response rate will be higher for patients with high tumor mutational burden (TMB, >10 mut/Mb) than for patients with low TMB (<10 mut/Mb) (by RECIST v1.1 and iRECIST)

## 9.2 SAMPLE SIZE DETERMINATION

The sample size for stage 1 is not based on formal statistical calculations. Rather, it is based on a desire to obtain sufficient safety and tolerability information while exposing as few patients as possible to the investigational treatments.

The sample size for stage 2 has been determined as follows. The currently available third-line treatment options for MSS mCRC are regorafenib and trifluridine-tipiracil, however ORR is <5% and improvements in PFS and OS minimal, if any (Appendix 4). As previously discussed, expected response to single agent treatment with either anti-PD-1 or EGFR inhibitor in this patient population is extremely poor (Appendix 12, including linked references). Efficacy data from currently available third-line treatment options for MSS mCRC will comprise an estimation of the historical control (null hypothesis): ORR 3%, DCR 45%, and 6-month PFS probability 20%. In this study, we estimate ORR 15%, DCR 65%, and 6-month PFS probability 40%.

In paired pre- and post-treatment biopsies in patients with lung cancer and head/neck cancer treated with evorpaccept (ALX148) and pembrolizumab, mean intra-tumoral pre- and post-treatment staining with CD68, CD163, and CD8 was 9 to 13%, 11 to 17%, and 8 to 10%, respectively. Based on this data, in this study, we will assume an expected mean of the paired differences of 5% with an expected standard deviation of the paired differences of 7%.

## 9.3 POPULATION FOR ANALYSES

All analyses will be conducted using the safety-evaluable population, defined as all patients who receive any amount of study drug. Exploratory efficacy analyses will also be conducted using the response-evaluable population (see Section 12.2 for definition).

## 9.4 STATISTICAL ANALYSES

### 9.4.1 GENERAL APPROACH

The primary analysis will be based on patient data collected through study discontinuation or at the end of study. All analyses will be conducted using the safety-evaluable population, defined as all patients who receive any amount of study drug. Exploratory efficacy analyses will also be conducted using the response-evaluable population (see Section 12.2 for definition).

Summary descriptive statistics will be calculated and presented for all primary, secondary, safety, and exploratory outcomes for all participants, and for stratifications defined by participant demographic characteristics. The demographic characteristics of the participants will be presented with descriptive statistics also. The means, medians, and 95% confidence intervals will

be calculated for continuous variables; the frequencies, estimated rates, and the exact 95% confidence intervals will be calculated for binary and categorical variables.

The safety, tolerability, and clinical activity of evorpaccept (ALX148), cetuximab, and pembrolizumab will be described and summarized, as warranted by sample size. That is, listings may be used in lieu of tables in the event of small sample size. Analysis of the primary efficacy, secondary efficacy, and exploratory endpoints will be performed as described in sections 9.4.2, 9.4.3, and 9.4.8, respectively. Safety analyses will be performed as described in section 9.4.4.

---

#### **9.4.2 ANALYSIS OF THE PRIMARY EFFICACY HYPOTHESIS & STOPPING CRITERIA**

The one-sided proportion test will be conducted for ORR against the null hypothesis that the ORR is less than or equal to 3%, with significance level of 0.05. The cumulative frequency, estimated proportion, and the exact 95% confidence intervals will be reported. A sample size of 48 achieves 87% power if the ORR is 15% using a one-sided exact test with a target significance level of 0.05. These results assume that the ORR of the historical control is 3%.

For  $\alpha = 0.025$  (1-sided) and power of 87%, MinMax design supports stopping enrollment for futility as noted if there are no responses (partial response or complete response as defined in the protocol) in first 24 subjects. Otherwise, full study enrollment will proceed as planned. Using a Simon-like 2-stage design, ORR will be determined based on the first 24 evaluable patients (including patients in both Stage 1 and Stage 2). If there are no responses (partial response or complete response as defined in the protocol) in the first 24 evaluable patients, then study enrollment will be stopped for futility. If there is at least one response (partial response or complete response as defined in the protocol) in the first 24 evaluable patients then full study enrollment will proceed as planned. If there are no responses (partial response or complete response as defined in the protocol) in the first 23 evaluable patients then enrollment will be temporarily paused to allow response evaluation of the 24th evaluable patient after up to 15 total weeks (ie 5 total cycles) of study therapy. If the 24th patient has response (partial response or complete response as defined in the protocol) then then full study enrollment will proceed as planned. If the 24th patient does not have a response (partial response or complete response as defined in the protocol) then the study will be stopped for futility. See Section 9.4.2 for statistical considerations.

---

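### Section 9.4.2 gives the primary ORR test two one-sided significance levels, 0.05 and 0.025, which require different numbers of responders if 56 to 60 patients are analysed

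*Protocol*

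**What the plan says.** Protocol section 9.4.2 covers the primary ORR analysis in two paragraphs.

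- **First paragraph, analysis.** "The one-sided proportion test will be conducted for ORR against the null hypothesis", which is worded as the "null hypothesis that the ORR is less than or equal to 3%, with significance level of 0.05".
- **First paragraph, power.** "A sample size of 48 achieves 87% power if the ORR is 15% using a one-sided exact test with a target significance level of 0.05". It adds: "The cumulative frequency, estimated proportion, and the exact 95% confidence intervals will be reported".
- **Second paragraph, two-stage design.** With alpha set at 0.025, the text continues "1-sided) and power of 87%, MinMax design supports stopping enrollment for futility as noted". The rule is to stop enrolment "If there are no responses (partial response or complete response as defined in the protocol) in the first 24 evaluable patients".

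No sentence says how 0.05 and 0.025 relate.

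The number of patients analysed is set elsewhere. Section 9.3 says "All analyses will be conducted using the safety-evaluable population, defined as all patients who receive any amount of study drug". Section 4.1.3 allows up to 18 patients in Stage 1, and section 4.1.4 enrols 42 in Stage 2. Sections 1.1 and 5.5 work with a total of 48, which section 1.1 calls the minimum.

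**The concern.** One primary test cannot have two significance levels. With an exact binomial test the conflict may be harmless, because the responder count moves in whole steps and one cut-off can satisfy both levels. Whether it is harmless depends on the number analysed, and version 2 of the protocol allows more Stage 1 patients than the six that make up 48 with Stage 2 (6 + 42).

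If the two levels give different cut-offs at the N reached, a single responder decides success or failure according to which sentence is applied. The trial is open-label and single-arm, so responses are visible as they accrue, and a level settled late would be settled with the data in view.

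**Working it through.** **Inputs.** From 9.4.2: p0 = 3%, p1 = 15%, N = 48, alpha 0.05 or 0.025 one-sided, futility stop at 0 responses in 24. From 9.3, 4.1.3 and 4.1.4: all treated patients, Stage 1 up to 18, Stage 2 of 42.

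**Formula.** For a cut-off of r responders, alpha = P(X ≥ r | N, 0.03) and power = P(X ≥ r | N, 0.15), with X binomial.

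**Step 1: the plan's own figure, N = 48, single stage.**

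| Cut-off | Alpha | Power |
|---|---|---|
| ≥4 | 0.0555 | 94.3% |
| ≥5 | 0.0143 | 86.6% |
| ≥6 | 0.0030 | 74.6% |

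The smallest cut-off with alpha at or below 0.05 is 5, and its 86.6% reproduces the stated 87%. Since 0.0143 is also below 0.025, both levels give 5.

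**Step 2: add the futility stop.** P(0 of 24) is 0.4814 at 3% and 0.0202 at 15%. Operating characteristic = P(X ≥ 5 | 48) − P(0 of 24) × P(X ≥ 5 | 24).

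- Alpha: 0.0143 − 0.4814 × 0.0006 = 0.0140.
- Power: 0.8656 − 0.0202 × 0.2866 = 0.8598.

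**Step 3: which level the interim belongs to.** A Simon minimax search for 87% power gives, at 0.025, 24 patients with a stop at 0, N = 49 and at least 5 responders (alpha 0.0151, power 87.1%). At 0.05 it gives 21 patients, N = 41 and at least 4 responders. The interim at 24 therefore fits 0.025, so that value does not look like a stray misprint.

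**Step 4: totals the protocol can produce.**

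- No further DLT: 6 already treated + 3 at dose level -1 + 3 at dose level 1 + 42 = 54.
- One DLT among the first 3 at dose level -1, none among the next 3: 6 + 6 + 3 + 42 = 57.
- Stage 1 ceiling: 18 + 42 = 60.

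**Step 5: exact cut-offs by analysed N.**

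| N | P(X≥4), p0 | P(X≥5), p0 | P(X≥6), p0 | Cut-off at 0.05 | Cut-off at 0.025 |
|---|---|---|---|---|---|
| 47 | 0.0521 | 0.0131 | 0.0027 | 5 | 5 |
| 48 | 0.0555 | 0.0143 | 0.0030 | 5 | 5 |
| 54 | 0.0786 | 0.0228 | 0.0055 | 5 | 5 |
| 55 | 0.0829 | 0.0244 | 0.0060 | 5 | 5 |
| 56 | 0.0872 | 0.0262 | 0.0066 | 5 | 6 |
| 57 | 0.0917 | 0.0280 | 0.0071 | 5 | 6 |
| 60 | 0.1057 | 0.0340 | 0.0091 | 5 | 6 |

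These tails rise with N, so the levels agree from 47 to 55 and part from 56 to 60.

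The cut-offs take no credit for the futility stop. With credit, N = 56 is a borderline case: 0.0262 − 0.4814 × 0.0025 = 0.0250, a shade under the limit. At N = 57 the conflict remains: 0.0280 − 0.4814 × 0.0029 = 0.0266.

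**Step 6: power at N = 60 with the stop.**

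- ≥5: 0.9576 − 0.0202 × 0.6450 = 0.9446.
- ≥6: 0.9032 − 0.0202 × 0.4594 = 0.8939.

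**The case against.** The best defence is that the two levels are compatible. The power sentence calls 0.05 a target, the 0.025 appears only in support of the futility stop, and the rule of at least 5 in 48 has an attained alpha of 0.014, which satisfies both. Sections 1.1 and 5.5 plan on 48, and even the path without further DLTs (54) leaves the cut-off at 5. All of this stands for N = 47 to 55. It does not cover 56 to 60, which the protocol's Stage 1 rules allow with Stage 2 fixed at 42.

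A reader might go further and infer that 4, 5 or 6 responders could be required depending on the sentence followed. The documents do not support that:

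- Four responders at N = 48 would need a normal-approximation reading of the proportion test. The protocol names no such test. The same paragraph specifies an exact test and an exact interval, and only the cut-off of 5 reproduces 87%.
- Six responders at N = 48 follows from no sentence. It arises only at the larger totals.

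Two further points are fair. A responder cut-off is often left to the analysis plan, so its absence is not a fault in itself; the fault is that two levels are stated. And which level to keep is the sponsor's choice, since 0.05 is stated twice for ORR and also used for the secondary tests in 9.4.3.

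**Conclusion.** The contradiction is real, and its effect is conditional. For 47 to 55 analysed patients it alters no decision. For 56 to 60 it is worth one responder: 5 responders give exact p = 0.028 at N = 57 and 0.034 at N = 60, a success at 0.05 and a failure at 0.025.

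This assumes that the primary test is the exact binomial, that all treated Stage 1 patients count as section 9.3 says, and that Stage 2 enrols its full 42. If the total were held at 55 or fewer (and not below 47), the difference would disappear.

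Two smaller matters follow. The 87% is the single-stage figure (86.6%); with the futility stop it is 86.0%. And at 0.05 with N = 56 or more, 5 responders would be declared a success although the exact two-sided 95% interval includes 3% (lower limit 2.9% at N = 57, 2.8% at N = 60). That follows from pairing a one-sided 0.05 test with a 95% interval and is not an error on its own.

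**What to change.** In section 9.4.2:

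1. State one one-sided alpha for ORR and use it in both paragraphs.
2. Call the analysis an exact binomial test in the sentence that prescribes it.
3. Give the responder cut-off by final analysed N:
   - if 0.025 is kept, at least 5 for N = 47 to 55 and at least 6 for N = 56 to 60;
   - if 0.05 is kept, at least 5 for N = 47 to 60, with the MinMax sentence corrected to match.
4. Replace 87% with the two-stage operating characteristics: for N = 48 and at least 5 responders, alpha 1.4% and power 86.0%.

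The cost is wording only. Choosing 0.025 loses no power for N = 47 to 55; at N = 60 two-stage power falls from 94.5% to 89.4%, still above the planned 87%. Choosing 0.05 keeps the 94.5% but accepts the interval mismatch described above. The choice should be recorded before further response data are reviewed.
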